#### Intent-to-treat analysis

These data will be analyzed using an intent-to-treat analysis. As H-Wave® Device is not widely utilized in study catchment area it is doubtful that individuals will inadvertently crossover to that arm from the controls. However, that possibility will be both discouraged and tracked.

#### Multiplicity

A multiplicity adjustment will be made for the comparison of the primary outcome variable, Oswestry Disability Index (ODI). The two-sided p values from the hypothesis tests will be adjusted for two comparisons using the Hochberg procedure [41]. With that procedure, the smaller of the two p values is compared against alpha = 0.025 and the larger p value is compared against alpha = 0.05. This maintains the overall alpha at 0.05 for the effectiveness win strategy evaluation.

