**Methods/Design:**

Patients- Chronic non-specific low back pain patients between ages of 18–65 years, with pain of at least 3 months duration and minimal current 5/10 VAS pain. Patients will have no significant signs or symptoms of lumbosacral nerve impingement, malignancy, spinal stenosis, or mood disorders.

Study design- Double blind RCT with 3 arms and 38 subjects per arm. Randomization by permuted blocks of random length, stratified by Workers Compensation claim (yes vs. no), and use of opioids. The null hypothesis of this study is that there are no statistically significant differences in functional improvement between treatment types during and at the end of a 12-week week treatment period.

Data collection- Subjective data will be collected using Filemaker Pro™ database management collection tools. Objective data will be obtained through functional assessments. Data will be collected at enrollment and at 1, 4, 8, and 12 weeks for each participant by a blinded assessor.

Interventions- H-Wave® device stimulation (Intervention A) plus usual care, transcutaneous electrical nerve stimulation (TENS) (Intervention B) plus usual care, and sham electrotherapy plus usual care (control). Each treatment arm will have identical numbers of visits (4) and researcher contact time (approximately 15 hours).

Outcomes- Primary outcome measure: Oswestry Disability Index. Secondary measures include: Rowland Morris Instrument, VAS pain score, functional evaluation including strength when pushing and pulling, pain free range of motion in flexion and extension. Outcome measures assessed at baseline, 1, 4, 8, and 12 weeks. Treatment failure will be defined if patient terminates assigned treatment arm for non-efficacy or undergoes invasive procedure or other excluded cointerventions. Data will be analyzed using intention-to-treat analysis and adjusted for covariates related to LBP (e.g. age) as needed.

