### Outcome measures

Outcome measures will be assessed at baseline, 1 week, 4 weeks, 8 weeks, and 12 weeks, with the primary outcome being at 4 weeks. Assessment will occur in the same manner and at the same time intervals for all treatment arms utilizing standardized methods. Treatment failure will be defined as if patient terminates assigned treatment arm for non-efficacy or election to pursue surgical or invasive procedure or other excluded cointerventions.

The primary outcome measure will be the Oswestry Disability Index (ODI). The ODI is widely used in low back pain intervention trials, and provides a measure of functional improvement The ODI was selected compared to a subjective pain rating [25-29]. Secondary outcome measures include Rowland Morris Instrument (0–24 scale of disability); VAS Pain score (0–100); physical activity levels objectively measured using accelerometers worn by participants during waking hours over during the entire 12 week study period; functional capacity evaluation including strength when pushing and pulling (3 repetitions lasting 5 seconds each of both pushing and pulling measuring both peak and average kg of force according to standard EvalTech Functional Systems protocol which utilizes a load cell to measure forces exerted); range of lumbar spine motion (up to participants maximum range of specific movement) in flexion, extension, lateral rotation; duration of time (minutes) sitting comfortably (subjective estimate made by participant during questionnaire); duration of time (minutes) standing comfortably (subjective estimate made by participant during questionnaire); duration (minutes) and distance (meters) walking comfortably (subjective estimate made by participant during questionnaire); summed VAS pain × days rating; days of impairment (days); lost workdays (days); time to exacerbation (days until increase 3/10 pain); rescue acetaminophen tablets consumed (% and number); NSAID discontinuation (%); opioid discontinuation (%). The pain VAS score is assessed immediately before and after treatment at weeks 0, 1, and daily scores pre and post home-treatment in a diary that the participant keeps (Table 1).

**Table 1 T1:** Outcome measures

	

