### Statistical approach

#### Statistical power/Sample size

Sample size determination is based on the comparisons of the study arms for the primary outcome variable, ODI. In previous studies of low back pain patients , the baseline ODI values for one study group were mean (SD) of 60.2 (15.0) and for a second study group were 59.9 (14.4) [39,40]. The total score for the ODI is a percentage, ranging from 0 to 100. It is suggested that the reliability of the ODI requires a minimum detectable change of at least 10 points, as any smaller difference may be attributable to error in the measurement [25]. Assuming equality of the study arms at baseline, which can be assured by adjusting for baseline ODI in the regression model, and a minimal detectable effect size of a 10 point difference on the post-treatment value, sample size is based on a comparison of mean (SD) of 60 (15) vs. 50 (15), a 17% relative difference post treatment, using a two-sided comparison with alpha of 0.025 to allow for multiplicity adjustment. Under these assumptions, a sample size of n = 43 subjects per study arm is required to achieve 80% power. However, it is expected that the stimulation arms will produce at least a 25% relative improvement over the control arm. Assuming 60 (15) vs. 45 (15), a 25% relative difference, using a two-sided alpha 0.025 comparison, a sample size of n = 20 subjects per study arm is required for 80% power, or n = 25 subjects for 90% power. Allowing for a 20% dropout rate, a sample size of n = 38 subjects will be enrolled in each study arm to provide n = 25 evaluable subjects for data analysis.

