### Statistical analysis

#### Primary analysis

The primary analysis is the comparison of the three study arms on the primary outcome, Oswestry Disability Index (ODI). Given that repeated measurements are collected, a mixed effects linear regression model will be fitted with an unstructured covariance matrix to account for lack of independence introduced by the repeated measurements. In this model, the repeated measurements are nested within study subject (weeks 0, or baseline, and weeks 1, 4, 8, and 12). The primary predictor is study group. A time variable will be included as a covariate, since visits will not always be at the planned intervals. Other covariates will be assessed for possible confounding in the relationship between treatment arm and outcome. It is likely that the pattern of dropouts will vary between the study groups, where the study interventions that are most effective having the dropouts later on in the follow-up, while the intervention least effective to have dropouts early on. The analysis will emphasize the 4-week time point as the primary end point, which ends the intensive intervention period. At 4 weeks compliance to the protocol and complete follow-up should be at a maximum. The remaining time to 12 weeks will measure long term effectiveness and acceptance of the study interventions.

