#### Secondary analyses

The changes from baseline to each follow-up visit in the pain VAS (the main secondary endpoint) will be analyzed using the same longitudinal model described above for the Oswestry score. Key secondary comparisons will include the three pair wise comparisons between the treatment groups in the mean change in the Roland Morris Instrument, VAS, strength, and flexibility measures at the different time points.,

The changes to 12 weeks will evaluate the persistence of treatment effects of the interventions to that time; changes to 4 weeks evaluate treatment effects at the completion of the intensive intervention period, and the slopes from weeks 4 to 12 evaluate changes in the treatment effects after 4 weeks. The null hypothesis is that there is no difference between the three treatment arms at 12 weeks.

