## Discussion

Chronic low back pain is a significant issue, resulting in significant costs, lost productivity, and morbidity [1-6]. Therefore, even small improvements in treatment efficacy, particularly for treatments with few side effects, can have a meaningful impact on improving LBP. While there have been some studies assessing the therapeutic effectiveness of TENS, the effect generally is relatively small improvements in chronic LBP as compared to sham treatment. The use of two comparison arms in this study, both TENS and sham treatment, allows for comparisons of experimental device with both TENS as well as sham treatment.

Blinding within this study is a significant strength. All devices are identical in appearance, weight, display, charge time, and sound. It is anticipated that complete blinding of the assessors and patients will be achieved. Care will be taken to limit contact between participants, e.g. schedule participants one at a time so they are not waiting in the same room together. All treatment questions will be directed to the interventionalists, as to maintain blinding of the assessors. Additionally, this protocol outlines concealing the treatment allocation by using opaque envelopes that appear identical. The utilization of a complex randomization schedule is another strength that may ensure equality of treatment groups at baseline. The intent-to-treat analysis may account for unequal dropout between groups and any contamination that may occur.

Potential weaknesses include the possibility of high dropout in one or more treatment arm. To combat this, we are offering incentives and encouraging participants to continue for the entire duration of the study. There is the possibility of a randomization failure, which cannot be overcome. Additionally, due to the nature of the treatment, specifically the differences between the experimental treatment and the TENS treatment, it was not feasible to blind the interventionalist. To address this all interventionalists will undergo strict training and re-standardization based on the treatment protocol. This training will stress treating all patients similarly with regards to demeanor and contact time, regardless of their randomized treatment arm.

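### The 5% overall error rate is claimed for two ODI comparisons that are never named, while three arms are compared and the text supports two different pairs

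*Protocol article*

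**What the plan says.** **Number of comparisons.** The Multiplicity section states that "The two-sided p values from the hypothesis tests will be adjusted for two comparisons using the Hochberg procedure". The smaller p value is set against 0.025, and "the larger p value is compared against alpha = 0.05". The section concludes that overall alpha stays at 0.05. It does not say which two comparisons are meant.

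**Arms compared.** The Primary analysis section says "The primary analysis is the comparison of the three study arms on the primary outcome". That gives three possible pairwise contrasts: H-Wave vs sham, TENS vs sham and H-Wave vs TENS.

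**Which pair.** Statistical power/Sample size uses a two-sided alpha of 0.025 per comparison, and "it is expected that the stimulation arms will produce at least a 25% relative improvement over the control arm". This points to H-Wave vs sham and TENS vs sham. The Discussion says the two comparison arms make a design that "allows for comparisons of experimental device with both TENS as well as sham treatment", which points to H-Wave vs TENS and H-Wave vs sham. The Abstract (Background) and the Background section frame the aim in the second way too.

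**Time point.** Outcome measures describes the assessments "with the primary outcome being at 4 weeks", and Primary analysis also calls week 4 the primary end point. The null hypothesis in the Abstract (Methods/Design) is "no statistically significant differences in functional improvement between treatment types during and at the end of a 12-week week treatment period". The only null in the statistical section stands under Secondary analyses: "The null hypothesis is that there is no difference between the three treatment arms at 12 weeks".

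**The concern.** An error-rate claim is meaningful only for a stated set of hypotheses. Here the document gives the number of tests, the thresholds and the resulting 5%, but not the hypotheses. H-Wave vs TENS, one of the trial's stated aims, is inside the protected family on one reading and outside it on the other. After unblinding, either pair could be reported as the planned one with the document cited in support. The mismatch between the abstract's null and the week-4 end point adds to the uncertainty about what the primary test is.

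The decision rule also reads as two separate threshold checks. Hochberg's procedure starts from the larger p value and rejects both hypotheses if it is at most 0.05. With p = 0.03 and p = 0.04, the written text rejects the hypothesis with the weaker evidence and keeps the one with the stronger.

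**Working it through.** **1. Inputs from the document.** Three arms; two adjusted comparisons; thresholds 0.025 and 0.05; claimed overall alpha 0.05; per-comparison alpha 0.025 in the sample size; SD 15; differences of 10 and 15 points.

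**2. The sample size reproduces.** The formula is n per arm = 2 × SD² × (z for alpha + z for power)² / difference², with z = 2.2414 for two-sided 0.025.
- Difference 10, 80% power: 450 × (2.2414 + 0.8416)² / 100 = 42.8, so 43.
- Difference 15, 80% power: 450 × 9.505 / 225 = 19.01, so 20.
- Difference 15, 90% power: 450 × (2.2414 + 1.2816)² / 225 = 24.8, so 25.

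All three match. The alpha of 0.025 fits a family of two comparisons.

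**3. The claimed 5% reproduces for a fixed pair.** For two independent tests, P(smaller p ≤ 0.025 or larger p ≤ 0.05) = (1 − 0.975²) + 0.025² = 0.049375 + 0.000625 = 0.0500. The contrasts here share an arm, so this was simulated (2,000,000 draws, equal arm sizes, normal statistics, no effect in any arm). Either pair gives 4.8%.

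**4. The same thresholds with the family left open, one visit, no effect.**

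| How the family is used | Chance of at least one false claim |
|---|---|
| One pair fixed in advance | 4.8% |
| Choice afterwards between the two pairs the text suggests | 6.7% |
| Two smallest of the three p values | 6.9% |
| Fixed pair, plus the third contrast at 0.05 | 8.7% |

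**5. The Hochberg wording.** The written rule and true Hochberg differ only when both p values lie between 0.025 and 0.05. Hochberg then rejects both; the text rejects only the larger p.
- With no effect this happens in about 0.15% of trials. The chance of any rejection is the same under both rules.
- With one true effect and one true null, the written rule is never more liberal beyond simulation error (for example 4.3% vs 4.4%). Both rules approach 5.0% when the true effect is very large.
- With 30 per arm, SD 15 and equal effects in both active arms, both p values fall in that band in 0.9% of trials (5 points), 1.2% (10 points) and 0.2% (15 points). With 25 per arm and 15 points it is 0.4%.

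The omission therefore costs a little power and can give an incoherent result. It does not raise the error rate.

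**The case against.** The strongest reply is that the document leans towards one pair. The sample size uses alpha 0.025 expressly for multiplicity and plans the effect of the stimulation arms over control, while the Discussion sentence says only what the design permits. A condensed article may also leave the naming of contrasts to an analysis plan. Part of this stands: each active device vs sham is the more natural reading, and the fix adopts it. But the Abstract and Background set H-Wave against both TENS and sham, so the conflict lies within the document. Having stated the number of tests, the thresholds and the 5%, it should say what is tested.

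A reader might infer three stronger points that the document does not support.

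- **That the Hochberg wording breaks the 5%.** It does not. The thresholds are right for two tests, and the incomplete rule rejects no more than the full one.
- **That success may be claimed at week 4 or week 12.** This would give 9.2% to 6.9% for a fixed pair, at an assumed between-week correlation of 0.3 to 0.9 (the document gives none). But Outcome measures and Primary analysis both make week 4 primary, and the 12-week null stands under Secondary analyses. What remains is a mismatch with the abstract's null, whose span includes week 4, and the absence of any null stated for week 4.
- **That the 5% is certainly lost.** It is kept if one pair at week 4 is fixed in advance. The rates above 5% describe use of the freedom that the text leaves open.

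**Conclusion.** The point holds in a limited form: the document does not secure the overall 5% that it claims. The claim is right (4.8%) for one named pair at week 4. It becomes about 7% if the pair is chosen afterwards and about 8.7% if the third contrast is also tested at 0.05. These figures assume equal arm sizes, normal test statistics and no effect in any arm, and they need no assumption about correlation between visits. The null statements are a matter of alignment, because week 4 is clearly primary. The missing step-up is a separate defect of wording that makes the rule slightly conservative. Since the error control of the primary claim depends on which contrasts are meant, they should be settled before unblinding.

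**What to change.** 1. In Multiplicity, name the two confirmatory week-4 ODI contrasts. H-Wave vs sham and TENS vs sham match the sample size.
2. Write the rule in full: if the larger p value is at most 0.05, reject both hypotheses; otherwise reject only the one with the smaller p value, and only if that is at most 0.025.
3. Report H-Wave vs TENS on the ODI as an estimate with a confidence interval and no confirmatory claim.
4. Align the null in the Abstract to week 4, and label the 12-week null under Secondary analyses as secondary.

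These are changes of wording and leave the sample size calculation as it is. The cost is that the contrast left outside the family carries no confirmatory claim.

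If the sponsor wants H-Wave vs TENS inside the family, there are two ways, and neither is only a matter of wording.
- **Three-step Hochberg over all three pairs** (0.0167, 0.025, 0.05) has a simulated error of 4.5% with no effect in any arm. At alpha 0.0167 the sizes become 48, 21 and 28 per arm instead of 43, 20 and 25.
- **An overall 2-df test at 0.05 followed by the three pairwise tests at 0.05** is a valid closed procedure for three arms, but it no longer matches the sample size calculation. With 25 per arm and 10-point effects in both active arms, the overall test passes in about 68% of trials. The chance of any rejection under the two-comparison Hochberg is 72.5%.

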#### Co-variates

Age, gender, tobacco, undiagnosed anxiety, undiagnosed depression, past back pain history, prior and current NSAID use, rescue acetaminophen use.

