**Secondary measures:**	
a.	Rowland Morris Instrument (0–24 scale of disability)
b.	VAS Pain score (0–10)
c.	Physical activity levels (objectively measured using accelerometers)
d.	Functional evaluation including strength when pushing (peak and average kg of force)
e.	Functional evaluation including strength when pulling (peak and average kg of force)
f.	Comfortable (up to maximum baseline pain level) range of motion in flexion (degrees from neutral)
g.	Comfortable (up to maximum baseline pain level) range of motion in extension (degrees from neutral)
h.	Duration of time sitting comfortably (up to maximum baseline pain level) (minutes)
i.	Duration of time standing comfortably (up to maximum baseline pain level) (minutes)
j.	Duration and distance walking comfortably (up to maximum baseline pain level) (minutes and meters)
k.	Summed VAS pain × days rating
l.	Days of impairment (days)
m.	Lost workdays (days)
n.	Time to exacerbation (days until increase 3/10 pain)
o.	Rescue acetaminophen tablets consumed (% and number)
p.	NSAID discontinuation (%)
q.	Opioid discontinuation (%)

Functional assessments will be completed using a standardized protocol on a BTE EvalTech system. Standard protocols for Lumbar Flexion/Extension, Lumbar Lateral Flexion, Shoulder Height Push and Pull, Cart Height Push and Pull are used. Researchers performing assessments are trained to perform all assessments exactly the same following the BTE EvalTtech protocol (Figure 2).

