### Usual care and co-interventions

Study participants will be asked to avoid significant changes in medical/healthcare management of their LBP during the study period. All participants will be allowed to pursue usual care with their own personal treating physician. No other treatment other than the assigned electrotherapy intervention will be provided by the trial researchers. Usual care will be limited to non-invasive therapies, including medications such as NSAIDS (prescription or over the counter) and opioids, physical therapy, manipulation, stretching and aerobic exercise. Self-applications of heat or ice are also acceptable. All usual care medications and interventions will be recorded.

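### Rescue acetaminophen use is a secondary outcome and also a listed covariate, and the confounding screen could bring it into the primary ODI model

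*Protocol article*

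**What the plan says.** The Co-variates section is a bare list that ends with "prior and current NSAID use, rescue acetaminophen use". It names no model and gives no time of measurement.

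The Primary analysis section fits a mixed model to ODI at weeks 0, 1, 4, 8 and 12, with study group as the main predictor and time as a covariate. It then adds: "Other covariates will be assessed for possible confounding in the relationship between treatment arm and outcome". The abstract (Methods/Design) says the data will be "adjusted for covariates related to LBP (e.g. age) as needed".

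The Outcome measures section names among the secondary outcomes "rescue acetaminophen tablets consumed (% and number); NSAID discontinuation (%); opioid discontinuation". Table 1 repeats rescue acetaminophen as item o and "NSAID discontinuation" as item p.

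Under Usual care and co-interventions, medication may continue during the trial: "Usual care will be limited to non-invasive therapies, including medications such as NSAIDS (prescription or over the counter) and opioids". It is also tracked: "All usual care medications and interventions will be recorded".

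The sections Intent-to-treat analysis and Other considerations commit the primary and main secondary analyses to comparison by randomised assignment.

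**The concern.** The same variable has two incompatible roles. As an outcome, rescue tablet use is something the devices are expected to influence. As a covariate in the ODI model, it is held fixed while the arms are compared. The coefficient then answers a different question: how the arms would differ among patients with equal rescue use. That is not the total effect of assignment, and randomisation does not protect it, because anything that drives both tablet use and disability within an arm is drawn into the comparison.

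The entry rule adds to the problem. If a device relieves pain, rescue use will probably differ by arm and will probably be related to ODI. Those are the two features by which a confounder is usually recognised. The variable is therefore most likely to be admitted when there is a real effect to estimate.

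**Working it through.** **1. What effect the plan is sized for.** The Statistical power/Sample size section uses SD 15, two-sided alpha 0.025, and differences of 10 or 15 points between arm means. With n per arm = 2 × (z₁ + z₂)² × (SD/difference)² and z₁ = 2.241:
- 10 points, 80% power: 2 × (2.241 + 0.842)² × (15/10)² = 42.8, so 43.
- 15 points, 80% power: 2 × (2.241 + 0.842)² × 1 = 19.0, so 20 after rounding up.
- 15 points, 90% power: 2 × (2.241 + 1.282)² × 1 = 24.8, so 25.

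All three stated figures reproduce. They describe a difference between arm means, adjusted at most for baseline ODI. That is a total effect, not an effect at fixed rescue use.

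**2. The passages side by side.** Outcome measures and Table 1 define rescue acetaminophen as tablets consumed, an outcome. Co-variates lists rescue acetaminophen use with no other definition. Primary analysis is the one place that describes how covariates reach the ODI model, and it excludes none. Nothing restricts rescue use to a baseline value or to exploratory models.

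**3. What adjustment does.** In a linear model, adding a post-randomisation variable changes the arm coefficient by

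change = d × r × s,

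where d is the shift in rescue use between arms (in SD), r is its within-arm correlation with ODI, and s is the SD of ODI. Only s = 15 is in the document; d and r are assumptions.
- d = 0.3, r = 0.3: 0.3 × 0.3 × 15 = 1.35 points.
- d = 0.3, r = 0.5, or d = 0.5, r = 0.3: 2.25 points.
- d = 0.5, r = 0.5: 3.75 points.

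This is 14% to 38% of a 10-point effect and 9% to 25% of a 15-point effect. If baseline ODI is also adjusted for, at an assumed correlation of 0.5, s falls to 15 × √(1 − 0.25) = 13.0 and the range becomes about 1.2 to 3.2 points.

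**4. A causal path through the tablets is not needed.** Suppose rescue use has no effect on ODI, but an unmeasured severity factor drives both: 5 ODI points per SD of severity, and a correlation of 0.5 between severity and rescue use. The within-arm slope is 5 × 0.5 = 2.5 points per SD of rescue use. A true 10-point effect is then estimated as 10 − 2.5 × 0.3 = 9.25 or 10 − 2.5 × 0.5 = 8.75. A simulation gave 9.3 and 8.7.

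**5. Direction.** The sign follows r. If heavier rescue use goes with worse disability (r positive) and the better arm uses less, the effect shrinks. If rescue use itself lowers ODI enough to make r negative, the same adjustment enlarges it.

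**6. Power, for illustration only.** At 25 per arm, a 15-point effect has 90.2% power. If adjustment absorbed 10%, 20% or 30% of it (assumed), 13.5, 12.0 or 10.5 points would remain, with power of 82.7%, 72.1% or 59.2%. This holds the SD at 15 and ignores any change in residual variance from the added covariate.

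**The case against.** Several stronger readings are tempting, and the document does not support them.

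- *Current NSAID use is a post-randomisation variable.* A reader might infer this from outcome p and from the NSAIDs allowed during follow-up. But the protocol uses *current* for status at enrolment in the opioid stratum (Randomization and allocation procedures) and in the eligibility criteria (Participants). On that reading, NSAID use is a legitimate baseline covariate, and NSAID discontinuation is a different variable. What stands is an ambiguity of timing.
- *The primary analysis will be biased.* The Co-variates list names no model, the screen is conditional, and the abstract's only example is age. Bias arises only if rescue use enters. What stands is that nothing keeps it out and the stated rule favours its entry.
- *The effect will be attenuated by a known amount.* The direction depends on an unknown correlation, and the ranges above rest on assumed inputs.
- *Covariates will be picked by how they move the treatment effect, so the p-values lose their meaning.* The protocol gives no selection criterion; a check of baseline imbalance is another reading, and model details are often left to an analysis plan that is not shown here. What stands is narrower: a screen for confounding of a randomised comparison is a poor rule, especially with a treatment-affected variable on its list.
- *Intent-to-treat is abandoned.* Patients are still analysed by assigned arm. What would change is the meaning of the adjusted coefficient.

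The core is not answered by any of these. An analysis plan could settle the details, but the protocol itself names an outcome as a covariate.

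**Conclusion.** The point holds for rescue acetaminophen. The protocol lists a declared secondary outcome as a covariate and gives a rule under which it may enter the primary ODI model. If it enters, the arm coefficient no longer estimates the total effect of assignment for which the trial is sized and which the intent-to-treat sections promise. Attenuation is likely when rescue use tracks pain, but it is not certain. The size cannot be derived from the document; the 1.35 to 3.75 points above show only what plausible-looking assumptions would give, and they are not an estimate for this trial. For NSAID use the finding is an undefined time of measurement and no more.

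**What to change.** - **Co-variates:** delete rescue acetaminophen use from the covariates of the primary and main secondary models. State that prior and current NSAID use means use before randomisation.
- **Primary analysis:** replace the confounding screen with a fixed list of baseline covariates, entered whatever the data show: the two stratification factors (opioid use and workers' compensation claim) plus the baseline variables chosen from the Co-variates section. Align the abstract's conditional wording with this.
- **Baseline ODI:** the sample size section expects adjustment for it, while the primary model already includes week 0 among the responses. Handle it once: either keep it as the week-0 response, or enter it as a covariate and remove week 0 from the outcome vector.
- **Rescue and on-study NSAID use:** analyse them only as outcomes.
- **Post-hoc analyses:** rescue acetaminophen also appears there as a possible predictor of response. Changing that is optional, because the analysis is labelled post hoc and does not touch the primary comparison.

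The cost is wording only: no change to data collection, visits or sample size.
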